# Effects of Supervised Early Resistance Training versus standard care on cognitive recovery following cardiac surgery via median sternotomy (the SEcReT study): protocol for a randomised controlled pilot study

**DOI:** 10.1186/s13063-020-04558-x

**Published:** 2020-07-15

**Keywords:** Median sternotomy, Resistance training, Cognition, Cardiac surgery, Recovery, Rehabilitation, Exercise

## Abstract

**Introduction:**

Mild cognitive impairment is considered a precursor to dementia and significantly impacts upon quality of life. The prevalence of mild cognitive impairment is higher in the post-surgical cardiac population than in the general population, with older age and comorbidities further increasing the risk of cognitive decline. Exercise improves neurogenesis, synaptic plasticity and inflammatory and neurotrophic factor pathways, which may help to augment the effects of cognitive decline. However, the effects of resistance training on cognitive, functional and overall patient-reported recovery have not been investigated in the surgical cardiac population. This study aims to determine the effect of early moderate-intensity resistance training, compared to standard care, on cognitive recovery following cardiac surgery via a median sternotomy. The safety, feasibility and effect on functional recovery will also be examined.

**Methods:**

This study will be a prospective, pragmatic, pilot randomised controlled trial comparing a standard care group (low-intensity aerobic exercise) and a moderate-intensity resistance training group. Participants aged 18 years and older with coronary artery and/or valve disease requiring surgical intervention will be recruited pre-operatively and randomised 1:1 to either the resistance training or standard care group post-operatively. The primary outcome, cognitive function, will be assessed using the Alzheimer’s Disease Assessment Scale and cognitive subscale. Secondary measures include safety, feasibility, muscular strength, physical function, multiple-domain quality of recovery, dynamic balance and patient satisfaction. Assessments will be conducted at baseline (pre-operatively) and post-operatively at 2 weeks, 8 weeks, 14 weeks and 6 months.

**Discussion:**

The results of this pilot study will be used to determine the feasibility of a future large-scale randomised controlled trial that promotes the integration of early resistance training into existing aerobic-based cardiac rehabilitation programs in Australia.

**Trial registration:**

Australian New Zealand Clinical Trials Registry (ANZCTR) ACTRN12617001430325p. Registered on 9 October 2017. Universal Trial Number (UTN): U1111-1203-2131.

## Introduction

### Background and rationale

Following cardiac surgery, mild cognitive impairment (MCI) affects 15–40% of patients, with the elderly affected at a greater rate [1–3]. This has the potential to become a significant health problem, as mild cognitive impairment is considered a precursor to dementia [4, 5]. Cardiac surgery patients are at a 30% risk of progression to dementia within 7.5 years of surgery [6] compared to 2.5% in the general population [5]. Following cardiac surgery, patients often require assistance with many activities of daily living; however, the personal and emotional cost of dementia is long lasting, including a loss of independence and self-control, strain on family and carers, depression and anxiety [7]. Furthermore, the economic cost of dementia in Australia, including hospitalisations, aged care costs and pharmaceuticals, was $14.25 billion in 2016, $8.8 billion (62%) of which involved direct costs to the healthcare system [7].

The cardiac surgery population is an ageing one with a general average age of 70 years old in most western countries and most present with multiple comorbidities [8]. Exercise, inclusive of aerobic and resistance training, can help to simultaneously manage numerous comorbidities; however, current cardiac rehabilitation programs are often of a low intensity and do not take into consideration a patient’s individual comorbidities and risk factors [9]. Furthermore, despite the high prevalence of cognitive impairment, cognitive recovery is not specifically assessed or considered in current cardiac rehabilitation programs, and the focus of programs to date has been on screening for depression, physical outcomes and at times functional outcomes [10].

It has been postulated that progressive resistance training augments the effects on insulin-like growth factor-1 and insulin sensitivity and mediates inflammation and neurotrophic factor pathways associated with cognitive decline and sarcopenia [11, 12]. Sarcopenia is a factor in increased falls risk, functional decline and frailty in this population [13]. Furthermore, a recent systematic review by Pengelly et al. found that the addition of resistance training to standard care, consisting predominantly of aerobic training, may lead to greater improvements in physical and functional post-operative recovery. However, it was identified that despite this finding, further research is required to investigate the safety and efficacy of specific resistance training following median sternotomy procedures and its effect on cognitive function [10].

Resistance training exercises have been reported to require focused and targeted coordinated input from, and blood flow to, all areas of the brain, which is believed to enhance neuroplasticity and neurogenesis [14, 15] at the levels of the central nervous system [11] and neurohormonal axis [12, 16].

Moreover, a recent review found that the performance of resistance training following median sternotomy appears to be safe and feasible, and results in similar improvements in both cardiopulmonary capacity and anthropometry, when compared to aerobic training alone [17]. Therefore, resistance training may be more effective at improving cognitive recovery beyond that of aerobic training alone. However, there are numerous problems with the translation and application of resistance training. This includes the misclassification of callisthenic-based exercises as resistance training; the resistance training programs do not meet the American College of Sports Medicine guidelines [18], and sternal stability has not been monitored prior to commencing or progressing upper limb exercises. Consequently, we do not know the effect of specifically designed resistance training interventions on post-operative recovery (i.e. in compliance with ACSM guidelines), nor has the effect of any mode of exercise on cognitive recovery in the surgical cardiac population been investigated [10, 17].

### Objectives

This study aims to examine the effect of moderate-intensity resistance training compared to a control group who receive standard cardiac rehabilitation involving low-intensity aerobic training within the community setting on post-operative cognitive recovery following cardiac surgery via median sternotomy. The safety, feasibility, patient satisfaction and effect of the exercise interventions on overall post-operative recovery, muscular strength, balance, lung capacity, upper limb function, independence with activities of daily living and anthropometry will also be examined. As this is a pilot study, the data obtained will be used to inform a sample size calculation to be performed for a larger definitive study.

## Methods

This prospective pragmatic pilot randomised controlled trial will be conducted in accordance with the National Statement on Ethical Human Research and the Australian Code for the Responsible Conduct of Research. Ethical approval has been granted from the Human Research Ethics Committee from Melbourne Health (Application ID: 2017.266). Local governance approval will be obtained prior to commencement of trial recruitment at other centres. All participants will provide written informed consent prior to commencing the study. The study follows the CONsolidated Standards of Reporting Trials (CONSORT) 2010 guidelines. This protocol includes the items identified in the Standard Protocol Items: Recommendations for Interventional Trials (SPIRIT) 2013 checklist (Additional file 1). The trial was prospectively registered with the Australian New Zealand Clinical Trials Registry (ACTRN12617001430325p).

### Study design and setting

The SEcReT study is designed as a multi-centre prospective pragmatic pilot randomised controlled trial with two parallel groups: (i) moderate-intensity resistance training and (ii) standard care, which involves low-intensity aerobic training. The SEcReT study will be conducted in Melbourne, Australia. Baseline measures will be obtained at T0 (pre-surgery) to allow comparison with post-operative outcomes (Fig. 1). The groups will then be assessed at T1 (day 1), T2 (day 3), T3 (day 6), T4 (2 weeks post-operatively/pre-intervention), T5 (8 weeks post-operatively/mid-intervention), T6 (14 weeks post-operatively/post-intervention) and T7 (6 months post-intervention) to examine the effect of the intervention on cognitive, physical and functional recovery.

**Fig. 1 Fig1:**
[figure not shown]
Flow diagram of study procedure, recruitments and randomisation

### Participants and recruitment

Participants will be recruited from the Royal Melbourne and Melbourne Private hospitals. Theatre and pre-admission clinic lists will be screened for patients undergoing cardiac surgery procedures via median sternotomy. Patients will then be approached about participating in the study and written informed consent provided prior to commencing data collection. Participants will be eligible if they meet the following inclusion criteria: (1) aged 18 years and older; (2) undergoing elective cardiac surgery via a median sternotomy, inclusive of coronary revascularisation and/or valve surgery; and (3) sufficient English to complete the questionnaires. If assistance to complete the questionnaires is required, the patient will be excluded from the study.

Participants with a dementia diagnosis, a musculoskeletal condition limiting ability to exercise or a geographical residence and/or lack of access to transportation, thus preventing exercise session attendance, will be excluded from this study. Furthermore, patients undergoing revision procedures that include a re-sternotomy will be excluded, as revision surgeries have been found to increase the risk of sternal complications, such as sternal infection and delay sternal healing [19]. There may also be an additional impact on sternal biomechanics, due to changes in sternal incision and bone integrity; however, this has not been investigated. Prior to commencement of data collection, written informed consent will be obtained from each participant.

### Randomisation, allocation concealment and blinding

All participants will be randomly allocated (1:1) to either the moderate-intensity resistance training group or the control group (standard care). Randomisation will be undertaken in blocks of 4–8, using double opaque envelopes. Envelopes will be prepared by an independent person not involved in the study. Patients will be randomised prior to discharge from hospital, following baseline data collection. The assessor is responsible for delivering the resistance training intervention, in addition to outcome measure assessment at all time points; therefore, she will not be blinded to group allocation. It will also not be possible to blind participants to their respective group allocation.

### Sample size determination

As this is a pilot study, a sample size calculation to determine the power of this study will not be performed. Instead, the focus will be on the feasibility and safety of the study. We plan to recruit a minimum of 20 participants, with an 80% retention rate.

The study schedule is outlined in Table 2, in accordance with the Standard Protocol Items: Recommendations for Interventional Trials (SPIRIT) figure. Participants will attend either The Royal Melbourne Hospital or Melbourne Private Hospital for baseline testing. This will include attainment of all outcome measures, excluding muscular strength, sternal stability and dynamic balance. During their hospital admission, quality of recovery will be assessed on the ward at T1, T2 and T3. Patients will then be randomised to either the (1) moderate-intensity resistance training intervention or (2) standard care group (control group). Strength and balance testing will be performed during the first post-operative visit, prior to commencing the allocated exercise intervention. This will occur approximately 2 weeks post-operatively. Patients in the resistance training group will attend Kieser Essendon, Caulfield or South Melbourne twice a week for 12 weeks (total of 24 exercise sessions). Patients in the control group will be referred to cardiac rehabilitation by their respective hospital, as per standard post-operative care procedures. All participants will be re-assessed at T5 (mid-intervention), T6 (post-intervention) and T7 (6 months follow-up). Patients will be contacted a week prior to their scheduled appointment to confirm attendance. Patients will also be told that they can contact the student researcher at any time during the study if they have any questions or concerns about their recovery. Cognitive assessments will be undertaken at T0 (baseline), T6 (post-intervention) and T7 (6 months follow-up).

**Table 2 Tab2:**
[figure not shown]
Study design schedule in accordance with the Standard Protocol Items: Recommendations for interventional Trials (SPIRIT). *MACCE* major adverse cardiac and cerebral events, *ADAS-cog* Alzheimer’s Disease Assessment Scale and cognitive subscale, *MMSE* Mini Mental State Examination, *IADL* Instrumental Activities of Daily Living, *PostopQRS* Postoperative Quality of Recovery Scale, *FDQ* Functional Difficulties Questionnaire, *FSST* Four Square Step Test

#### Withdrawals and replacements

Participants will be informed that they are free to withdraw from the study at any time. They will also be informed that their withdrawal will not affect the relationship between them and the treating doctors or the hospitals. They will be informed that any data collected to point of withdrawal will be used to prevent bias in the results, unless they specifically refuse that request. From the time of withdrawal, no further data will be acquired for that participant.

Participants will not be replaced if they withdraw from the study. Data collected to point of withdrawal will be used to prevent bias in the results. As this is a pilot study, this data is required to determine study feasibility and group separation and will represent a low risk of bias to the study.

### Exercise intervention

#### Moderate-intensity resistance training group

Participants randomised to the moderate-intensity resistance training group will receive an exercise program to be performed twice a week for 12 weeks. The program will initially include 6 exercises targeting the lower limbs, upper limbs, neck and back, with an additional exercise added after the first week. Following the T6 (mid-intervention) assessment, patients will progress to a program consisting of 11 exercises (see Table 3). The exercise program will include the following exercises: leg press, knee extension, knee flexion, hip abduction, hip adduction, latissimus pulldown, shoulder press, seated row, triceps extension, biceps curls, lateral raise, lumbar extension and neck (cervical) extension. The exercise sessions will be delivered by a qualified exercise physiologist. Participants will be instructed to perform the exercises at a 4-2-4 tempo; that is, 4 s concentric contraction, 2 s isometric hold, 4 s eccentric contraction. Participants will be instructed to complete a single set until volitional fatigue or will be instructed to stop by the exercise physiologist when technique falters. When working at a moderate intensity, each exercise will be performed for a period of 90–120 s, or 9–12 repetitions.

**Table 3 Tab3:** Details of the resistance exercises and exercise progression

	Exercise	Target muscle group(s)	Sets x Reps	Intensity	Progression
**Weeks 1–6**					
1	Knee extension*	Quadriceps	1 × 9–12	RPE 13–16/20	Progressed by 5–10% of the initial weight until patients are able to exercise within the desired range (RPE 13/20 or volitional fatigue after 9–12 repetitions)
2	Knee flexion*	Hamstrings			
3	Bicep curl	Biceps			
4	Lateral raise	Deltoids			
5	Triceps pushdown	Triceps			
6	Back extension**	Lumbar extensors			
7	Neck extension	Cervical extensors			
**Weeks 7–12**					
1	Leg Press	Gluteals, hamstrings and quadriceps	1 × 9–12	RPE 13–16/20	Progressed by 5–10% of the initial weight until patients are able to exercise within the desired range (RPE 13/20 or volitional fatigue after 9–12 repetitions)
2	Hip abduction	Hip abductors			
3	Hip adduction	Hip adductors			
4	Latissimus pulldown	Latissimus dorsi			
5	Shoulder press	Deltoids and trapezius			
6	Seated row	Latissimus dorsi, trapezius, deltoids			
7	Bicep curl	Biceps			
8	Lateral raise	Deltoids			
9	Triceps pushdown	Triceps			
10	Back extension**	Lumbar extensors			
11	Neck extension	Cervical extensors			

*Progressed to Leg Press in weeks 7–12, **progressed from 0–45° to 0–55° trunk flexion in weeks 7–12

*RPE* Rating of perceived exertion

##### Exercise protocol

Measures of sternal micromotion of the sternal edges will be acquired by ultrasound imaging during each upper limb exercise with a 20-lb. resistance (the lightest weight), prior to commencing the resistance training intervention session. Sternal stability will also be assessed prior to the exercise intervention by physical examination and using the Sternal Instability Scale (SIS) [31]. If an increase in sternal micromotion > 2 mm is detected from rest and coughing, upper limb resistance training will not be commenced, or progressed, if sternal micromotion is detected with an increase in resistance. If no increase in sternal micromotion is detected, patients will continue with the initial starting weight of 20 lb. until they are familiar with the exercise equipment and technique. Participants will perform each exercise until volitional muscle fatigue, completing between 9 and 12 repetitions or achieving a rating of perceived exertion (RPE) of 13–16/20 on the Borg scale [36].

##### Exercise progression protocol

The 12-week program will be divided into two phases. For the first week, participants will commence with 6 exercises. From weeks 2–6, an additional exercise will be added (Additional file 2). After the T5 (mid-intervention) assessment, exercises will be progressed from open kinetic chain exercises using isolated single muscle movements to large compound movements using multiple muscle groups. The final 6 weeks of the program will consist of 11 exercises, each performed until volitional muscle fatigue and progressed according to the aforementioned progression protocol (Additional file 3). Additional weight will be progressively added in increments of 5–10% of the initial weight (1–2 lb. for upper limb exercises, 4–10 lb. for lower limb exercises) until patients are able to exercise within the desired range (RPE 13/20 or volitional fatigue after 9–12 repetitions).

##### Pain-level documentation and cessation of exercise rules

Pain will be defined as an increase in pain from the initial pain rating as a direct result of an exercise and assessed using the Numeric Rating Scale (0–10). An exercise will be immediately ceased with reports of sternal pain or discomfort, any sharp increase in pain or adverse event.

##### Adverse events

Adverse events will be classified as adverse events (AEs) or serious adverse events (SAEs). An AE will be defined as an incident that requires the cessation of exercise for safety reasons and is likely to be directly related to the exercise program. If an adverse event is life-threatening, requires hospitalisation and results in significantly reduced capacity or disability, or death, it will be classified as a SAE. This will be inclusive of new or unrelenting chest pain, any report of shortness of breath that does not settle quickly with rest, or acute changes in level of consciousness during the session will be considered as serious adverse events. Any serious adverse event will be immediately reported to the Ethics Committee. If there is an unacceptable risk of serious adverse events in one or both of the treatment groups, the trial will be stopped and termination may be recommended by investigators.

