#### Secondary outcomes

##### Safety and feasibility

Recruitment rate and retention rate will be analysed to determine study feasibility. Feasibility data will be analysed as follows: recruitment rates and patient recruitment-to-screening ratio, percentage of participants who complete the intervention, overall percentage of sessions attended and number of participants who drop out of the study. Data for safety will be analysed as the number of sessions and exercises stopped due to pain, any adverse event or incident that stops the participant from completing the prescribed exercise, and any major adverse cardiac and cerebral events (MACCE). MACCE endpoints include all-cause mortality, cerebral vascular event (stroke), documented myocardial infarction or repeat coronary intervention (percutaneous coronary intervention or redo cardiac surgery), with data being collected at the 6 months.

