### Data analysis

The objective of this pilot study is to test the feasibility of recruitment, retention, intervention and data collection, and the safety of moderate-intensity resistance training, on post-operative cognitive and functional recovery. The following parameters would indicate clinically important relative differences between groups:
Group separation: ≥ 20% difference between groups;Feasibility: screening-to-recruitment ratio < 2 and recruitment of ≥ 1 participant/site/week;Safety: adverse events and serious adverse events;Protocol compliance: ≥ 80% protocol compliance and exercise intervention commenced at two post-operative weeks;ADAS-cog: difference of at least 2 on the ADAS-cog scale; andMuscular strength: ≥ 15% improvement in strength.

The analysis will be on an intention-to-treat basis. Data collected for feasibility and safety will be analysed using descriptive statistics (mean ± standard deviation) to explore possible effects of the intervention. Mean changes in outcomes over time will be summarised graphically and descriptively within each group, with odds ratio and confidence intervals. As this is a pilot study, it is not powered to detect clinically meaningful effects. Feasibility data will be analysed to determine whether it is worth conducting a large-scale trial. A statistician not involved in the study and the student researcher will assess these parameters at the end of the trial.

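### Adverse events are defined only through exercise, so AE and SAE counts are not comparable between arms; the SAE criteria also need reconciling with the sentence that follows them

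*Protocol article*

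**What the plan says.** All references are to the protocol article.

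- **AE (Adverse events).** "An AE will be defined as an incident that requires the cessation of exercise for safety reasons". The same sentence then adds a second condition: "and is likely to be directly related to the exercise program". The two conditions are joint.
- **SAE (same section).** "If an adverse event is life-threatening, requires hospitalisation and results in significantly reduced capacity or disability, or death, it will be classified as a SAE". The next sentence adds chest pain and unsettled breathlessness, and ends: "acute changes in level of consciousness during the session will be considered as serious adverse events". The section closes with a rule that stops the trial if SAE risk is unacceptable in either or both groups.
- **Safety data (Safety and feasibility).** The plan counts the "number of sessions and exercises stopped due to pain, any adverse event or incident that stops the participant from completing the prescribed exercise", together with MACCE: "MACCE endpoints include all-cause mortality, cerebral vascular event (stroke), documented myocardial infarction or repeat coronary intervention", including redo cardiac surgery.
- **Use (Data analysis).** The list of parameters marking important differences between groups includes "Safety: adverse events and serious adverse events". No threshold is attached, and the analysis is descriptive.
- **Exposure.** Procedure and data collection gives the resistance arm two sessions a week for 12 weeks, 24 in all, delivered by an exercise physiologist. Standard care group describes a typical program of one session a week for 6 weeks, reached by referral to a hospital or community provider.
- **Assessor (Randomisation, allocation concealment and blinding).** The person who assesses outcomes also delivers the resistance training and is not blinded.

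**The concern.** Safety is one of the two things this pilot says it focuses on, and its results are meant to inform a larger trial. An event definition that depends on exercising, and on being attributed to exercise, measures different things in the two arms. One arm is watched by the trial at every session. The other exercises elsewhere, and the article states no route by which its session events reach the study.

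The error can run in either direction. Session-linked events will tend to accumulate in the resistance arm because it has more sessions and is observed. Harm that appears between sessions can drop out of the AE and SAE counts altogether, which would be falsely reassuring about early loading after sternotomy. Attribution is part of the definition, so any judgement of relatedness made by unblinded staff decides whether an event exists, not only how it is labelled.

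The same counts feed two stated uses: the between-group safety parameter and the trial-stopping rule.

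**Working it through.** The article states no AE rate and no safety sample size, so there is no planned figure to reproduce. The one checkable count agrees with the text: 2 per week × 12 weeks = 24 sessions.

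**1. What the definitions catch.** Illustrative events set against the text:

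| Event | AE? | SAE? | Captured elsewhere? |
|---|---|---|---|
| Wound infection or fall between sessions, not attributed to exercise | No | No | Not as an event |
| Readmission between sessions for a non-MACCE cause, not attributed to exercise | No | No | Not as an event |
| Stroke between sessions, not attributed to exercise | No | No | MACCE |
| Sternal separation found at a study visit, no exercise stopped | No | No | Sternal stability measures |
| Exercise-related stop, hospitalised, no lasting impairment, none of the listed symptoms, not life-threatening | Yes | No, read literally | Stopped-session count |
| Exercise-related stop for breathlessness that does not settle, no admission | Yes | Yes, by the symptom sentence | Stopped-session count |

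The last two rows show the inconsistency: an admission can fail to be serious while a symptom without admission is serious. If cessation of exercise is read to include giving up the whole program, some events in the first two rows meet the first condition, but attribution to exercise is still required.

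**2. Exposure by arm.** Inputs: minimum 20 participants (Sample size determination), 1:1 allocation, hence about 10 per arm; 24 and 6 sessions per participant; full attendance assumed.

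- Resistance: 10 × 24 = 240 sessions.
- Control: 10 × 6 = 60 sessions.
- Resistance share of definable AEs at equal per-session risk: 24 / (24 + 6) = 80%. Equal proportional attendance in both arms leaves this unchanged.
- Equal expected counts would need a per-session risk in the resistance arm of 6/24 = one quarter of the control risk.

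**3. What this does to counts.** Per-session risk p is an assumption, taken equal in both arms, with sessions independent. Expected events = sessions × p; chance of at least one = 1 − (1 − p)^sessions.

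| p | Expected, resistance v control | At least one, resistance v control |
|---|---|---|
| 0.2% | 0.48 v 0.12 | 38% v 11% |
| 0.5% | 1.2 v 0.3 | 70% v 26% |
| 1% | 2.4 v 0.6 | 91% v 45% |
| 2% | 4.8 v 1.2 | 99% v 70% |

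With 8 per arm (80% retention) and p = 1%, the figures are 1.92 v 0.48 expected, and 86% v 38%.

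**4. Adding under-observation of controls.** If only a fraction c of control session events reaches the study, the resistance share is 24 / (24 + 6c): 80% at c = 1, and 24/27 = 89% at c = 0.5. The documents give no value for c.

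**The case against.** The strongest reply is that other planned measures cover much of the ground. MACCE at 6 months is restricted neither by arm nor by relation to exercise, and includes death from any cause. Table 1 lists sternal ultrasound and the Sternal Instability Scale at 2, 8 and 14 weeks and 6 months without an arm restriction. The Sternal stability text limits the exercise-specific checks to the resistance arm but keeps cough ultrasound in both groups at 6 months. The upper-limb questionnaire and the recovery scale, with its nociceptive domain, are repeated in all participants. Stopped sessions and exercises are counted without an attribution condition. Controls attend the same reassessments and may contact the researcher, and adverse outcomes go to the ethics committee. Capture procedures may be set out in a full protocol that is not shown.

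This reply stands in part, and it rules out four stronger readings that a reader might infer:

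- *That most harms go uncounted.* No harm rates are given, so the share cannot be computed.
- *That sternal harm is missed in both arms.* Sternal stability has a planned measurement in both, although an infection without instability does not.
- *That the control count is near zero by construction.* Controls exercise too, and the definition is not limited to one arm. The count is structurally lower, not shown to be nil.
- *That every SAE criterion is joined by 'and'.* Only hospitalisation and reduced capacity or disability clearly are. Death is an alternative, the place of life-threatening events is unclear, and listed symptoms qualify alone. The 'and' may be a drafting slip.

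The reply does not remove the central point. None of these measures changes what counts as an AE or SAE, and it is those counts that the between-group parameter and the stopping rule name. The definition is stated outright, so it is not a detail left to another document.

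**Conclusion.** The concern holds in this limited form: as defined, AE and SAE counts are not comparable between arms. At equal per-session risk and full attendance, with 6 control sessions as typical, about 80% of definable AEs would fall in the resistance arm, and more if control events are less often observed. Non-MACCE harms arising outside exercise are not counted as AEs in either arm, in unknown proportion. The SAE sentence, read literally, excludes some hospitalisations and does not fit the symptom sentence beside it.

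Severity is moderate. The safety analysis is descriptive, in a pilot of about 20 with no test and no threshold, so the damage is to the by-arm description, to the input to the stopping rule, and to what the larger trial would inherit.

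**What to change.** - **AE.** Define it in both arms as any untoward medical occurrence from randomisation to T7, with relatedness recorded as a separate item. The article places T7 both six months after the intervention and six months after surgery, so state the end of the window explicitly.
- **SAE.** Make the criteria alternatives by using 'or', and reconcile them with the symptom sentence.
- **Ascertainment.** Ask the same AE questions in both arms at the existing T4 to T7 visits.
- **Tolerability.** Report stopped sessions and exercises separately, as a resistance-arm measure, outside the between-group comparison.
- **This trial.** Recruitment ended on 31 August 2019. Reclassify events from available records where possible; otherwise report the by-arm AE and SAE counts as non-comparable. Do not carry the definition into the larger trial.

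The cost is a wording change, a short question set at visits already scheduled, and slightly more AE recording. Reclassification adds a record review for about 20 participants.
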